#### Design and procedures

This research proposal has gained approval from the Human Research Ethics Committee of [blinded university]. Written informed consent will be obtained from all participants' parents or legal guardians before the initiation of the study. Parents or legal guardians will be asked to complete a set of questionnaires on family demographics, children's characteristics and executive functioning. Prior to the training, children will first complete a pre-test in a quiet room at the University. Then, children will be randomly assigned to either the (a) egocentric block building or (b) altercentric block building training group. The training period will be six weeks, with a 1.5-h training session per week. The training will be conducted in a child-friendly lab at the University. After the training sessions are completed, the children will be tested with the same battery of measures in the post-test. Upon completion of the training, the participants' parents or legal guardians will receive a report of their child's performance and a gift voucher valued at HKD$200.

#### Measures

Raven’s Coloured Progressive Matrices (RCPM; [92]) is a non-verbal reasoning test that measures the general cognitive ability of young children aged 4 to 11 years. The RCPM consists of three sub-tests (Set A, AB, B); each subtest has 12 items. For each item, the administrator presents an incomplete design and children are asked to find the missing part of the design from six options to complete the design. The items are arranged in ascending order of difficulty in each subtest. The ascending difficulty levels also apply to the subtests, where Set A is the easiest and Set B the most difficult. A score of one will be given for each correct answer. The maximum possible score is 36, where higher scores indicate a higher level of nonverbal reasoning abilities.

The Bear/Dragon task [93] assesses the executive function of behavioural inhibitory control in young children. This task is a simplified version of the Simon Says task, in which children are required to selectively obey or ignore specific commands according to the rules given by the experimenter. Two stuffed animals, a bear and a dragon, will first be introduced to the children. Then the administrator will instruct the children to follow action commands such as “touch your head” given by the bear, and ignore the ones given by the dragon. After practice, there are 10 randomized trials of the bear and dragon commands. Children’s responses will be assigned a score from 0 to 3 in each dragon trial (0 = full movement, 1 = partial movement, 2 = wrong movement, and 3 = no movement). The maximum possible score is 15, where a higher score indicates better ability in behavioural inhibitory control.

The Hong Kong Test of Preschool Oral Language (Cantonese) (TOPOL-EV; [94]) assesses young children’s oral language abilities in the preschool period (i.e., from 2 years 6 months to 5 years 11 months of age). The expressive vocabulary subtest will be used in this study. The expressive vocabulary subtest consists of 58 items. In each item, the administrator presents one picture and children are required to name the displayed picture. Five categories of vocabulary are tested in this subtest, such as stating the objects or the actions. The items are arranged in ascending order of difficulty. A score of one will be given for each correct answer. The maximum possible score is 58 and higher scores indicate better knowledge of Cantonese expressive vocabulary.

The Test of Early Mathematics Ability-3 (TEMA-3) [95] measures early informal and formal mathematics skills in children aged from 3 to 8 years 11 months. The test consists of 72 age-based items, and the items for age 4 (i.e., 8 items) will be used in this study. Ryoo et al. [96] categorized the 72 items into different categories, and the items for age 4 were grouped into five categories, including:Counting objects, e.g., 'How many stars did you count?'Calculation, e.g., 'Make your tokens just like mine by adding up 1 + 1 tokens'Set construction, e.g., 'Can you give me 5 tokens?'Verbal counting, e.g., 'Counting tokens from 1 to 10'Numeral literacy, e.g., 'What is this number?'

Each item will be scored with children’s binary response (i.e., fail = 0 or pass = 1). The maximum possible score is 8, where high scores indicate better early mathematics abilities.

The 3D Test of Spatial Assembly (TOSA) [87] measures the general spatial abilities of children aged 3 years and above. The TOSA consists of 7 test items. In each item, children are presented with a model assembly with different individual LEGO blocks. They are required to re-create the model with the same number of blocks given to them. Each model has a base piece, i.e., the largest piece or the piece that is connected to the greatest number of other pieces, and component pieces, i.e., other pieces. Children are scored based on the accuracy of three aspects, including the correct vertical location of the pieces, the correct rotation of the pieces, and the correct placement of the pieces over block pips. The spatial test uses a two-step scoring system, including: (1) base piece scoring (i.e., pieces with spatial relationships and dependent on the base piece) and (2) subset scoring (i.e., pieces with spatial relationships and independent of the base piece). A score of 1 is given for every correct assembly. The maximum possible score is 14 (7 items for each scoring step). A higher score indicates better spatial abilities.

The Perspective-Taking Test for Children (PTT-C) [97] assesses children's ability to represent the viewpoint of others. This test is based on the seminal Three Mountains Task by Piaget and Inhelder [98]. The PTT-C consists of 3 practice items and 18 testing items. Children are presented with a colour printout showing a toy photographer taking pictures of one or two 3D objects from different angles with each item. Then, children are asked to choose the picture among four options that the toy photographer would have taken. One of the pictures shows the correct view, and the other three are foils that include the same objects but with different orientations or spatial relationships. The items ascend in difficulty (one object to two objects) and vary in the angular disparities between the children and the toy photographer (0°, 90°, or 180°). A score of 1 is given to each correct response. The maximum possible score is 18. Higher scores indicate better visuospatial perspective-taking skills.

The Test of Emotion Comprehension (TEC) [99] assesses understanding of emotion in children aged 3 to 11 [100]. The TEC comprises nine subtests: recognition, external causes, desire, belief, reminder, hiding, mixed, and morality. This study will administer five of the subtests age-appropriate for 4.5-year-old children, including external cause (5 items), a score is given when at least 4 out of 5 are correct; desire (4 items), a score is given when all are correct; belief (1 item), reminder (1 item), and hiding (1 item), a score is given when it is correct. In each item, children are presented a cartoon scenario with a gender-matched protagonist. These story scenarios should elicit different emotional responses in the protagonist. Children are then given four cartoon faces, each representing an emotional state (happiness, sadness, anger, fear, or normal). They are asked to speculate the emotional state of the protagonist in response to the event. The maximum possible score is 5. Higher scores indicate better emotion understanding.

The Theory-of-Mind Scale (ToMS) [89] measures children’s ability to understand different mental states (e.g., desire, knowledge, belief). The ToMS consists of seven interactive tasks, including diverse desire, diverse belief, knowledge access, content false belief, explicit false belief, and hidden emotion. In each task, children are presented with a story with props (e.g., puppets, band-aid box, toy carrot) and are asked questions regarding their own mental states and those of the target protagonists. A score of one is given to each correct answer. The maximum possible score is 5 and a higher score indicates a more advanced level of mental state understanding.

#### Training activities

The children will be randomly grouped into pairs, and a trained experimenter will guide them. All the experimenters will receive a three-hour training on the block-building training protocol. The training sessions will be videotaped and carefully reviewed; the experimenters will be given corrective feedback to ensure consistency of the instructions and guidance given to different pairs of children. Training trials vary in model complexity (2, 3, or 4 blocks in the model figure) and in seating position (see Table 1).

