## Research plan and methodology

### Study 1: examining the role of visuospatial perspective-taking in developing theory of mind and emotion understanding

#### Participants

Participants will consist of 96 typically developing Cantonese speaking 4.5-year-olds (48 males; 48 females). The targeted age group is 4.5-year-old children because the ontogenetic development of both ToM and emotion understanding abilities typically emerges at around 4 to 5 years of age [89].

This study will investigate the effect of visuospatial perspective-taking training on children’s ToM and emotion understanding abilities by capitalizing on their mind-understanding differences at this age. Several meta-analyses have reported moderate to large effect sizes for ToM, emotion understanding, and relevant spatial training [43, 90, 91]. The effect size of this study can thus be reasonably estimated as medium-to-large. We used G*Power 3.1 to conduct an a priori power analysis to determine the required sample size. Results indicated that a total sample of 79 participants was required to achieve a power of 0.80 for detecting a medium-to-large effect (*f* = 0.32) at an alpha of 0.05 for a MANOVA (MANOVA: Repeated measures, within-between interaction). To account for a potential attrition rate of 20%, we propose to recruit 48 children per group, thus 96 children in total, via electronic fliers on local internet groups.

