#### Data analysis plan

First, we will perform correlation analyses with the pre-test data to examine the associations among visuospatial perspective-taking and ToM and emotion understanding. We hypothesise that there will be positive relationships among preschoolers' visuospatial perspective-taking, ToM, and emotion understanding.

We then will use independent *t*-tests to test the group differences in nonverbal reasoning, inhibitory control, and oral language proficiency and decide if these three variables will be used as covariates in subsequent analysis. Next, we will use repeated measures ANOVAs to examine the post-training improvements in general spatial and mathematics skills in both groups. Previous research has illustrated a positive effect of block-building on preschoolers’ spatial and mathematics skills [83, 84, 86, 87]. We will also examine if the altercentric block-building group improves significantly more than the egocentric block-building group in visuospatial perspective-taking. This will ensure that the altercentric training increases visuospatial perspective-taking that we aim to train.

In the main analysis, we will use repeated measures MANOVAs to determine the post-training changes in understanding mind and emotion across the two groups. We predict that the altercentric block-building group will show greater improvements in ToM and emotion understanding abilities than the egocentric block-building group. Moreover, these improvements will be mediated by the improved visuospatial perspective-taking ability.

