### Study 2: Comparing the roles of visuospatial perspective-taking and verbal interaction in developing theory of mind and emotion understanding

#### Participants

This study will compare the effects of three different training methods on the development of mind and emotion understanding in preschool children. Participants will consist of 120 typically developing Cantonese-speaking 4.5-year-olds (60 males; 60 females), with 40 children in each training group. We used G*Power 3.1 to conduct an a priori power analysis to determine the required sample size. Results indicated that a total sample of 98 participants was required to achieve a power of 0.80 for detecting a medium-to-large effect (*f* = 0.32) at an alpha of 0.05 for a MANOVA (MANOVA: Repeated measures, within-between interaction). To account for a potential attrition rate of 20%, we propose to recruit 40 children per group, thus 120 children in total, via electronic fliers on local internet groups.

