#### Data analysis plan

The preliminary analyses will be the same as those in study 1. Next, repeated measures MANOVAs will be conducted to compare the effectiveness of the three trainings in improving children’s visuospatial perspective-taking, ToM, and emotion understanding abilities. We predict all of the training in study 2 will increase children’s ToM and emotion understanding. In particular, we hypothesise that the *socialised altercentric block building* training will result in the greatest improvement on the children’s ToM and emotion understanding. We expect the paired dialogic reading to enhance children’s general language ability but not their visuospatial perspective-taking ability. In contrast, we expect that the *parallel altercentric block building* will enhance the children’s visuospatial perspective-taking ability but not their general language ability. We further hypothesise that the *socialised altercentric block-building* training will enhance both visuospatial perspective-taking and language abilities because verbal interaction may strengthen children’s developing ability to simulate the visuospatial experience of others. This finding will reveal whether visuospatial perspective-taking is conducive to developing ToM beyond the contribution of verbal interaction.

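### Children are trained in pairs, but the MANOVAs and both sample sizes treat them as independent; any positive intra-pair correlation makes the tests too liberal and the stated 0.80 power too high

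*Protocol article*

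**What the plan says.** The Training activities section of each study states: "The children will be randomly grouped into pairs, and a trained experimenter will guide them". Training runs for six weekly sessions of 1.5 hours. The partner matters to the task. In Study 1 the altercentric-frame task is defined by the partner's viewpoint, and some trials have the children change seats. In group (a) of Study 2, pair-mates are encouraged to talk about the toy bear's perspective. Random assignment is described at the level of the child.

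The Study 1 Data analysis plan says "we will use repeated measures MANOVAs to determine the post-training changes in understanding mind and emotion across the two groups". The Study 2 plan says "repeated measures MANOVAs will be conducted to compare the effectiveness of the three trainings", for visuospatial perspective-taking, ToM and emotion understanding.

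The Participants sections base the sample size on "detecting a medium-to-large effect (*f* = 0.32) at an alpha of 0.05" with a repeated measures MANOVA routine. In Study 1 "a total sample of 79 participants was required to achieve a power of 0.80"; in Study 2 "a total sample of 98 participants was required to achieve a power of 0.80". The only inflation is for attrition, in Study 1 as follows: "To account for a potential attrition rate of 20%, we propose to recruit 48 children per group, thus 96 children in total". Study 2 applies the same 20% and recruits 120. The sample-size text and the analysis plans mention no pair, intra-pair correlation or design effect.

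**The concern.** Two children who share a partner, a table, an experimenter and up to nine hours of training (6 × 1.5) may come to resemble each other in how much they change. Where they do, a group mean based on n children carries less information than n independent scores. A MANOVA on individual children then understates its standard errors, and the power routine overstates power.

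The article names the test, the power routine, alpha, effect size and N, and those choices do not match the delivery format it also fixes. Both primary comparisons are affected, in the anti-conservative direction, in a project that aims at a causal conclusion. In Study 2 the dependence may also differ between the discussing and the parallel block-building arms, a contrast the study is built to examine.

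**Working it through.** **Inputs from the article.** f = 0.32, alpha = 0.05, two time points, k = 2 groups (Study 1) or 3 (Study 2). Required N is 79 and 98; recruited N is 96 and 120; attrition is 20%; cluster size is 2.

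**Assumed.** The ICC of pre-post change within a pair is not given. The range taken is 0.05 to 0.30, with pairs kept for all six sessions.

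**Step 1: reproduce the stated sizes.** For the named routine with two time points, df1 = k − 1, df2 = N − k and λ = f²N.
- Study 1: λ = 0.1024 × 79 = 8.09, df (1, 77), power 0.802. The smallest N reaching 0.80 is 79.
- Study 2: λ = 0.1024 × 98 = 10.04, df (2, 95), power 0.804. The smallest N reaching 0.80 is 98.

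Both match exactly, and both assume independent children.

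**Step 2: design effect.** With pairs it is 1 + (2 − 1) × ICC = 1 + ICC. The true standard error exceeds the naive one by √(1 + ICC): 1.02, 1.05, 1.10 and 1.14 at ICC 0.05, 0.10, 0.20 and 0.30.

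**Step 3: power when pairs are respected**, with λ divided by 1 + ICC:

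| N analysed | ICC 0 | 0.05 | 0.10 | 0.20 | 0.30 |
|---|---|---|---|---|---|
| Study 1, stated 79 | 0.80 | 0.78 | 0.76 | 0.73 | 0.69 |
| Study 1, 76 completers | 0.79 | 0.77 | 0.75 | 0.71 | 0.68 |
| Study 1, all 96 | 0.87 | 0.86 | 0.84 | 0.81 | 0.78 |
| Study 2, stated 98 | 0.80 | 0.78 | 0.76 | 0.72 | 0.69 |
| Study 2, 96 completers | 0.80 | 0.77 | 0.75 | 0.71 | 0.68 |
| Study 2, all 120 | 0.88 | 0.87 | 0.85 | 0.82 | 0.78 |

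Completers are 0.8 × 96 = 76.8 (76 used) and 0.8 × 120 = 96. Pair-level degrees of freedom (N/2 − k) lower each entry by a further 0.01 to 0.02. These figures are for the routine as stated, which is a single-outcome test.

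**Step 4: type I error of the MANOVA that ignores pairs.** Simulated Pillai tests on change scores at nominal 0.05, with 38 per arm (Study 1) and 32 per arm (Study 2), whole pairs, and the same ICC on every outcome:

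| Test | ICC 0 | 0.05 | 0.10 | 0.20 | 0.30 |
|---|---|---|---|---|---|
| Study 1, two outcomes | 0.050 | 0.058 | 0.065 | 0.081 | 0.102 |
| Study 2, three outcomes | 0.049 | 0.059 | 0.071 | 0.097 | 0.134 |

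Repeat runs differ by about 0.005 or less. For a single outcome the inflation is smaller. In Study 1 the approximation 2 × [1 − Φ(1.96/√(1 + ICC))] gives 0.062, 0.074 and 0.086 at ICC 0.10, 0.20 and 0.30. In Study 2 a simulated single-outcome test reaches 0.100 at ICC 0.30.

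**Step 5: does a random pair intercept repair it?** Write the score of child i in pair j at time t with a pair effect u_j that is constant over time. The change (post minus pre) subtracts u_j from itself, so it drops out of the arm-by-time contrast. A simulation with 38 per arm and change-score ICC 0.30 confirms this. The mean standard error was 0.2666 with the time-constant pair intercept, 0.2666 with pairs ignored, and 0.303 from pair means. The ratio 0.303/0.2666 = 1.14 equals √1.30.

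**The case against.** A reader might infer that pairs are fixed for the whole training period and that inflation is therefore certain. The article supports neither step. It says only that children are grouped into pairs at random, and re-pairing between sessions would change the dependence and remove the simple factor 1 + ICC. Children are randomised individually and paired at random, so pair-mates bring no shared history. Any correlation must come from the training itself, and at ICC 0 the MANOVA keeps its 5%. The planned video review and corrective feedback should also reduce differences between pairs. These points stand, and they make the conclusion conditional.

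The size is also limited. Clusters of two give a design effect of at most 1.30 over the assumed range. The 13% figure needs an ICC of 0.30 on all three outcomes. Part of the power gap at completers is attrition: with no clustering, power is already 0.786 at 76 (against 0.802 at 79) and 0.795 at 96 (against 0.804 at 98).

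Finally, this is a condensed article, and an unseen analysis plan could add a pair term. That may answer the analysis half. It does not answer the power half, because the published 0.80 was calculated for independent children.

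**Conclusion.** The point holds in conditional form. Delivery in pairs is stated; the MANOVA and the sample sizes of 79 and 98 assume independence. With any positive intra-pair correlation the tests are too liberal and 0.80 is too high. Over an assumed ICC of 0.05 to 0.30 with lasting pairs, type I error is about 6–10% (Study 1, two outcomes) and 6–13% (Study 2, three outcomes). Power is about 0.78–0.69 at the stated N, and 0.77–0.68 at 76 and 96 completers against 0.79 and 0.80 without clustering. If nobody drops out, power stays at about 0.81 at ICC 0.20 and falls to 0.78 at 0.30. The type I inflation does not depend on attrition. The article gives no ICC, so these are ranges under an assumption, not estimates for this trial.

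**What to change.** - State whether pairs stay together over the six sessions, and record a pair identifier for every child. The article does not say that one is kept.
- Account for pair in the main analysis of change. One option is pair-clustered standard errors with a small-sample correction. The other is a mixed model for the baseline-adjusted post-test, or for the change score, with a random pair effect. In a long-format pre/post model the pair effect must be pair-by-time, because a time-constant pair intercept leaves the arm-by-time standard error uncorrected (step 5). If separate models per outcome replace the joint MANOVA, say how the two or three outcomes are handled for multiplicity.
- In Study 2, use arm-specific pair variances only as a sensitivity analysis. There are 40/2 = 20 pairs per arm at enrolment and about 32/2 = 16 after 20% attrition if whole pairs leave, too few to estimate them well.
- Restate power with the factor 1 + ICC over a stated ICC range, at the existing enrolment.

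The cost is a few sentences of plan text, one recorded variable, a slightly less favourable power figure and slightly wider intervals. Training and enrolment do not change.

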**Table 1 Tab1:**
[figure not shown]
The gradation of difficulty in block-building training in study 1

Three types of seating positions exist during the *altercentric frame* time in the block-building training, including:change seats with the partner and reproduce the model figure from the partner’s visual framechange seats with the partner for ten seconds and return to the original seat to reproduce the model figure based on the partner’s visual frameimagine how the model figure looks from the partner’s viewpoint and reproduce the model figure based on the partner’s visual frame.

The block-building training activities are described below:

**Table Taba:** 

*Egocentric block building *training (control group; Fig. 1)	The block building training follows the training procedures from Verdine et al. [87]. The children are seated next to each other at the play table. The experimenter then presents a model figure built from blocks and places it at the center of the play table. The training begins with the *egocentric frame* time, in which children are instructed to reproduce the same block figure from a group of scattering blocks based on their own visual frame. The *altercentric frame* time follows, in which children are instructed to reproduce the block figure that looks the same from their partner’s point of view. Since the participant’s partner sits next to them, the block figure should look largely the same to the participant’s line of sight. The difficulty of building these block figures is age-appropriate for children aged 3–5 years [87]
(b) *altercentric block building* training (experimental group; Fig. 2)	In this training group, the children are seated opposite to each other at a play table. The training begins with the *egocentric frame* time, with the same procedure as the *egocentric frame* time of training (a). The *altercentric frame* time follows, during which the children try to adopt the visual frame of their play partner who is sitting on the opposite side of the play table. They will be instructed to imagine how the model figure looks for their partner and build a figure that looks the same from their partner's viewpoint. Since the participant’s partner seats opposite to them, the figure should have 180° angular difference to the participant’s line of sight

